#### Primary outcome

##### Functional capacity

Consistent with previous physical activity interventions targeting youth with disability,^37^ our primary outcome is functional capacity, assessed using the 6MWT,^38^ which has good reliability in adolescents with disability (ICC=0.82).^27^ The 6 min push test will be used for students who self-propel a wheelchair.^39^ Students will be instructed to cover as much distance as possible in 6 min, and the distance (in metres) covered will be documented.

#### Secondary outcomes

##### Physical activity

Participants will be instructed to wear an ActiGraph GT9X Link accelerometer on their non-dominant wrist for 24 hours/day (even when bathing, swimming and sleeping) for a period of seven consecutive days (3 days’ minimum wear time). School hour, weekday and weekend (ie, mean minutes per day) physical activity will be calculated separately, using existing thresholds for categorising physical activity intensity.^22^

##### Muscular fitness

Lower body muscular endurance will be assessed using the 30 s sit-to-stand test.^40^ From a seated position, students will attempt to stand up and sit back down on a 44 cm high bench seat as many times as possible in 30 s.^18^ A modified version of the 90° push-up test will be used to assess upper body muscular endurance.^41^ All students will be instructed to perform as many push-ups as possible on their knees.

##### Body composition

Body weight and height will be measured using a portable digital scale (A&D Medical UC-352-BLE Digital Scales) and a portable stadiometer (Seca 213 Portable Height Measuring Rod Stadiometer), respectively. Body mass index (BMI) will be calculated using the standard formula (weight[kg]/height[m]^2^). Age-specific and sex-specific BMI z-scores will be calculated, and participants will be classified into weight categories according to International Obesity Task Force cut-offs.^42^

##### Cognitive function

This will be assessed with electronic tablets using the cognitive portion of the National Institutes of Health (NIH) Toolbox.^43^ The Toolbox has been used with children and adults with Fragile X syndrome, Down syndrome and intellectual disabilities, with tests demonstrating good to excellent reliability and feasibility.^43 44^ Participants will complete the Flanker (inhibition), list sorting (working memory), and dimensional change card sort (cognitive flexibility) tasks.

##### Quality of life

Health-related quality of life will be assessed using the Child Health Utility 9-Dimensions,^45^ which includes nine items (worried, sad, pain, tired, annoyed, schoolwork or work, sleep, daily routine and activities), and each item is scored on a five-point scale.

##### Physical literacy

Autonomous motivation for physical activity will be assessed using identified and intrinsic subscales from the ‘Behavioural Regulations in Exercise Questionnaire-2’.^46^ Confidence will be assessed using the validated six-item High-Intensity Interval Training Self-efficacy Questionnaire.^47^ Competence will be assessed using video analysis of a selection of skills from the Resistance Training Skills Battery (ie, push-ups, lunge, squat and front support chest touch), which has been validated among typically developing adolescents^48^ and among children with varying degrees of motor skill proficiency.^49^

##### Externalising behaviours

Teachers will complete a Student Behaviour Questionnaire^50^ for each student at baseline, 6 months, and 9 months. The questionnaire consists of 10 statements, regarding students’ classroom behaviours, observed over the previous 6 months, which are rated using a 3-point Likert scale. The items have been adapted from the strengths and difficulties questionnaire externalising subscale.

##### On-task behaviour

To determine the acute effect of the B2La intervention on students’ behaviour in the classroom, observations will be conducted by trained research assistants at baseline and midintervention (3 months) using established methods.^51^ The assessment includes a 30 min observation period where research assistants will assess the on-task and off-task behaviour of six randomly selected students (5 min per student). Observation and recording are completed in 15 s intervals (20 observations per student), and teachers and students will not know who is being observed during the assessment.

### Economic evaluation

We will assess the efficiency and affordability of the intervention using cost-effectiveness/cost utility analysis and budget impact, respectively, conducted from a public finance perspective. The effectiveness measure will be based on the primary outcome (6MWT). Transformation of the Child Health Utility 9-Dimensions data will be employed in a cost utility analysis. The resource use and costs for the intervention and usual practice will be prospectively measured and derived from project records (staff and consumables), teacher surveys and school records. Additional costs in the intervention group are anticipated to be labour (implementation support), programme development and training costs. The cost-effectiveness analysis will be conducted on a ‘within trial’ basis, that is, over the 6-month study period, comparing incremental costs and outcomes. Affordability of the programme will be calculated using budget impact analysis, over a standard accounting cycle and is designed to assist decision making in schools and hence assist the translation of cost-effective and affordable programmes. Scenario analysis will assess the costs to implement the programme at scale across NSW. Reporting for the economic analysis will adhere to the Consolidated Health Economic Evaluation Reporting Standards (CHEERS) statement.^52^

### Process evaluation

We will conduct a process evaluation to determine programme acceptability, implementation, adaptability, and sustainability in schools.

#### Acceptability

We will conduct focus groups to determine teachers’ and participants’ (ie, students) perceptions of, and experiences with, the intervention. Teachers will also complete the Acceptability of Intervention Measure, Intervention Appropriateness Measure, and Feasibility of Intervention Measure.^53^

#### Implementation

Teachers will be asked to record their delivery of B2La sessions using the teacher handbook. We will also track the number of sessions delivered using the B2La smartphone app. Members of our research team will conduct two session observations (using the SAAFE checklist) at each school to determine intervention fidelity. Finally, participants’ mean heart rate during sessions will be collected using the B2L app.

#### Adaptability

Teachers will be asked to reflect on how they adapted the intervention in the focus groups. This will include adaptions in relation to the characteristics of the school, class, and students.

#### Sustainability

Sustainability will be explored in the focus groups and via teacher and participant postprogramme evaluation questionnaires. Teachers will report their intention to deliver B2L in the future and complete an adapted version of the Program Sustainability Assessment Tool.^54 55^ Students will report their intention participate in HIIT in the 2 months following programme completion.

### Statistical analyses

Blinded analyses of the primary and secondary outcomes will be conducted by an independent statistician, using linear mixed models SAS V.9.1 (SAS Institute Inc), with alpha levels set at p<0.05. The models will be used to assess the impact of group (B2La or control), time (treated as categorical with levels baseline, 6 months and 9 months) and the group-by-time interaction. The models will include a random intercept for participant to account for the repeated measures for each participant and a random intercept for school to account for the clustered design. The primary endpoint of the study will be 6 months from baseline. Least square mean differences between the treatment groups will be presented at both follow-up time points, with 95% CIs and p values. Compared with complete case analyses, mixed models include available data for all participants and are thus both more efficient and robust to bias. Mixed model analyses are consistent with the intention-to-treat principle, assuming the data are missing at random. The validity of this assumption will be explored by assessing relationships between missingness and observed values. We will conduct two sensitivity analyses for the primary outcome: (1) multiple imputation (assuming data are missing at random) and (2) complete case analysis (assuming data are missing completely at random). Four potential moderators (ie, socio-economic status, sex, initial weight status and disability type) will be explored using interaction terms (ie, time-by-treatment-by-moderator). If an interaction term is significant (p<0.1), sub group analyses will be conducted.

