### Sample size and power calculation

Power calculations were based on the primary outcome of functional capacity, assessed using the 6 min walk test (6MWT), which has good reliability in adolescents with disability (intraclass corelation coefficient (ICC)=0.82).^27^ A 6 min push test will be administered for wheelchair users. Although adolescent data are lacking, studies conducted among adult populations with chronic health conditions have reported minimal clinically important differences (MCID) of 24–44 m using the 6MWT.^28^ In our pilot study, we observed a large increase in distance covered from baseline to immediately after the intervention period (163±131 m). However, our pilot study did not include a control group, and effects are typically smaller in effectiveness trials compared with pilot studies.^29^ Based on the pilot data, we estimate a treatment effect of 80 m will represent a MCID in our population. Through simulations (n=10 000) and using data from our pilot study (ie, baseline post-test correlation of *r*=0.60, SD of 90 m and an ICC of 0.2), we have determined we will require a sample of 30 schools with seven participants per school. This sample size will be enough to detect an MCID of 80 m with 90% power at a 5% significance level. Allowing for 30% loss to follow-up at 6 months, we will aim to recruit 10 students from 30 schools (total sample size of 300).

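### A time-constant school intercept drops out of the baseline-to-6-month group-by-time contrast, so that test is too liberal if schools change differently over time

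*Protocol article*

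**What the plan says.** All of the model text is in the Statistical analyses section of the protocol article.

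- Fixed effects: group, "time (treated as categorical with levels baseline, 6 months and 9 months) and the group-by-time interaction".
- Random effects: "The models will include a random intercept for participant to account for the repeated measures for each participant and a random intercept for school". The stated purpose of the school term is "to account for the clustered design".
- Reported estimates: "Least square mean differences between the treatment groups will be presented at both follow-up time points, with 95% CIs and p values".
- Test level: "alpha levels set at p<0.05". Sidedness is not given; I take it as two-sided.

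No school-by-time effect, cluster-robust variance or basis for degrees of freedom is named. The Sample size and power calculation section gives an "SD of 90 m and an ICC of 0.2" and a baseline/post-test correlation of 0.60, for 30 schools with seven analysed students each. It gives no separate ICC or variance for school-level change.

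**The concern.** Under the stated model a school's deviation is identical at baseline, 6 months and 9 months. Subtracting baseline from 6 months removes it, along with the participant intercept. What remains as error for "the group-by-time interaction" is the student-level residual, and the contrast is judged as if 210 students had been randomised one by one.

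The Blinding and randomisation section allocates schools, not students. If students in one school tend to change together, that shared change is error at the level of randomisation, and the model has no place for it. The article gives reasons to expect some. Two teachers per school facilitate the sessions, teachers are encouraged to adapt exercises, adaptation to school and class is a process outcome, control schools follow their own usual practice, and mainstream support classes are mixed with schools for specific purposes.

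At stake are the false-positive rate and the interval width for the interaction on the primary outcome, and on every secondary outcome analysed with the same model.

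**Working it through.** **Inputs (Sample size and power calculation):** SD 90 m (variance 8100), r = 0.60, ICC 0.2, 15 schools × 7 = 105 students per arm, two-sided 5%.

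**The plan's own figures.** 210/0.7 = 300 reproduces the recruitment target. The design effect is 1 + 6 × 0.2 = 2.2. For a 6-month comparison on the raw SD, SE = 90 × √(2 × 2.2/105) = 18.4 m, so 80 m has 99.1% power (normal) or 98.7% (t, 28 df). The stated aim to "detect an MCID of 80 m with 90% power at a 5% significance level" is therefore not reproduced: the inputs give more. That is a separate matter and does not affect what follows.

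**Step 1: SE of the change contrast under the planned model.**
Variance of change per student: 2 × 8100 × (1 − 0.60) = 6480.
With no clustering penalty: 6480 × 2/105 = 123.4, so SE = 11.1 m.

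**Step 2: SE when schools change differently.** Let c be the correlation of a school's effect between waves (assumed; the article gives none). The school variance is 0.2 × 8100 = 1620, so the school-level change variance is 2 × 1620 × (1 − c). The ICC of change is ρ = that value/6480, and the design effect needed is 1 + 6ρ.

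Example, c = 0.8:
- School change variance 2 × 1620 × 0.2 = 648; student part 6480 − 648 = 5832.
- True variance (2/15)(648 + 5832/7) = 197.5, so SE = 14.1 m.
- The planned model's estimate is 122.7 on average, marginally below 123.4. The SE ratio is √(197.5/122.7) = 1.27.
- The real critical value is 1.96/1.27 = 1.54, which corresponds to a type I error of about 12%.

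**Step 3: range of c.** The simulated sizes come from two independent sets of null trials (30 × 7, three waves); at 0.95 only one set was run.

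| c | ρ | Design effect needed | Planned SE (m) | True SE (m) | Simulated size |
|---|---|---|---|---|---|
| 1 | 0 | 1.00 | 11.1 | 11.1 | 5.1–5.2% |
| 0.95 | 0.025 | 1.15 | 11.1 | 11.9 | 6.9% |
| 0.9 | 0.05 | 1.30 | 11.1 | 12.7 | 8.4–9.5% |
| 0.8 | 0.10 | 1.60 | 11.1 | 14.1 | 11.7–12.3% |
| 0.6 | 0.20 | 2.20 | 11.0 | 16.5 | 18.4–18.7% |

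The analytic sizes for c = 0.9, 0.8 and 0.6 are 8.6%, 12.2% and 18.9%. A school-level t test of change, which allows for school-by-time variation, holds 4.8–5.8% throughout.

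**Step 4: the other contrast.** For the least squares mean difference at 6 months, the true variance is (2/15)(1620 + 6480/7) = 339.4, SE 18.4 m. The school intercept does enter here. With 28 df the planned model reports about 18.3 m at c = 1, falling to 16.9 m at c = 0.6. The simulated size is about 5–7% for c from 1 down to 0.5.

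**Step 5: power with school-by-time variation allowed for.** For a true 80 m effect, the school-level analysis of change has simulated power of 99.2% at c = 0.5 and essentially 100% at c = 0.8 and 1.

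**The case against.** **The reported p value may not be the interaction.** The only estimates promised with intervals and p values are the least squares mean differences at each follow-up. Read literally, these are differences at that time point, and their size is close to nominal. This stands, and it limits the point to the interaction test. It does not clear that test, which the plan also says it will assess. Nor does the article say which contrast is primary. The 6-month difference does not use the baseline value, although the power calculation uses the baseline/post-test correlation; that costs precision, not validity.

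**The size rests on an assumption.** This stands too. At c = 1 there is no inflation, and at 0.95 it is about two percentage points.

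**Teacher delivery varies only in intervention schools during the trial.** Partly right. If only that arm had school-specific change, the excess would be about halved: at c = 0.8 the average design effect is (1.6 + 1)/2 = 1.3, a size of about 8.6%. Control schools also have their own practice, so their change variance need not be zero.

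**Matching may offset the error.** Schools are randomised in matched pairs, and the article names no pair term for the model. With an assumed within-pair correlation of 0.3 in school effects, simulation gives 7.2%, 9.4% and 14.8% at c = 0.9, 0.8 and 0.6, against 8.4%, 12.1% and 18.2% unpaired. The 6-month difference falls to 3.3–4.1%. Inflation of the change test is reduced, not removed.

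**The remedy is detail for an analysis plan.** This is fair for the exact degrees-of-freedom method and any convergence fallback, which are not criticised here. The random terms themselves are stated in the article.

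**Conclusion.** The point holds in conditional form. The stated random structure does not protect the baseline-to-6-month group-by-time contrast against school-specific change. If such change exists, the SE is too small and the type I error exceeds 5%: about 7% at a cross-wave school correlation of 0.95, 8–10% at 0.9, 12% at 0.8 and 18–19% at 0.6. This rests on the plan's SD, r, ICC and 30 × 7, on equal school-by-time variance in both arms, and on no gain from matching. The correlation itself is assumed.

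A reader might infer that the trial's primary p value is certain to be too small. The article does not support that: it gives no school-by-time variance, and the p value may come from the 6-month mean difference, where the size is about 5–7%. A reader might also take it that all students of a school are tested in one sitting, adding shared test-day error. The article gives term windows and assessors but does not say so, and the point does not need it.

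If the true effect is near 80 m the conclusion would not change, since power exceeds 99% on the change contrast either way. The harm is false positives and intervals that are too narrow.

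**What to change.** 1. Add a random school-by-time effect, or an equivalent school-level covariance over waves, to the primary and secondary models.
2. Base the degrees of freedom for the treatment contrasts on the number of schools: about 28 if schools are treated as unmatched, fewer if a pair term is used.
3. State which 6-month contrast is the primary test: the difference in change from baseline or the difference at 6 months.

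The cost is one extra random term, a degrees-of-freedom option and one sentence. Intervals on the change contrast become somewhat wider: by a factor of about 1.06 at c = 0.95 and 1.26 at c = 0.8, with almost no change if schools do not differ in their change. No extra schools or students are needed; on the printed inputs, power for 80 m on that contrast stays above 99%.

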## Methods

### Study design

Our trial is registered with the Australian New Zealand Clinical Trials Registry (ACTRN12621000884808). The reporting of this trial will adhere to the CONSORT^25^ guidelines. The B2La intervention will be evaluated using a two-arm parallel group cluster randomised controlled trial (RCT) with a treatment group and waitlist control group. Assessments will occur at baseline, 6 months (primary endpoint) and 9 months from baseline (secondary endpoint). The RCT will be conducted with two cohorts, one starting in 2022 (10 schools; five intervention and five control) and another starting in 2023 (20 schools; 10 intervention and 10 control). Baseline data collection will occur in the school term preceding intervention delivery (ie, term 1 (February–April 2022 and 2023). The intervention will be delivered during terms 2, 3 and 4 (April–November 2022 and 2023). Immediate postintervention data collection (ie, ~6 months) will occur at the end of term 3 (August–September 2022 and 2023), and follow-up assessments (ie, ~9 months) will be completed in term 4 (November–December 2022 and 2023).

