### Blinding and randomisation

Randomisation will occur within each cohort once consenting schools have completed baseline assessments. Schools will be matched as closely as possible based on the following characteristics in this order: (1) school type (ie, mainstream school support class/SSP), (2) school sector (ie, government/Catholic/independent), (3) geographic location (ie, region, rural/urban, coastal/inland) and (4) student population educational advantage (ie, using the Index of Community Socio-Educational Advantage).^30^ Matched schools will be randomised to the intervention or waitlist control group using a random number producing algorithm by an independent statistical analysis service – Clinical Research Design, Information Technology and Statistical Support run by the Hunter Medical Research Institute. One school from each pair will be allocated to the B2La condition and the other to the waitlist control condition. Schools randomised to the intervention group will deliver the B2La programme during the study period, whereas schools allocated to the waitlist control group will continue with usual school practice (ie, normal curricular lessons) for the duration of the study period and will receive the intervention the following year. We decided to use a waitlist control design, rather than an attention-matched placebo because: (1) our research team will have minimal contact with students, and (2) our findings will have greater external validity, as participants in the control group will receive ‘usual practice’.

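### Schools are randomised within matched pairs and cohorts, but the primary model has no pair, matching-factor or cohort term; if the matching is effective, the 6-month interval will be wider than it need be

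*Protocol article*

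**What the plan says.** Under Blinding and randomisation, the protocol article states: "Randomisation will occur within each cohort once consenting schools have completed baseline assessments". It continues, "Schools will be matched as closely as possible based on the following characteristics in this order", and lists school type (mainstream support class or school for specific purposes), sector, geographic location and educational advantage. Then: "One school from each pair will be allocated to the B2La condition and the other to the waitlist control condition". Study design plans 10 schools for 2022 and 20 for 2023, half in each arm. That makes 15 pairs, 5 in the first cohort and 10 in the second.

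Under Statistical analyses the model terms are listed: "The models will be used to assess the impact of group (B2La or control), time" and their interaction, with a random intercept for participant and "a random intercept for school to account for the clustered design". Pair, matching factors and cohort do not appear. Socio-economic status, sex, weight status and disability type enter only as exploratory moderators. On reporting: "Least square mean differences between the treatment groups will be presented at both follow-up time points, with 95% CIs and p values". The sample size section does not mention pairing.

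**The concern.** Matching makes the arms alike on the matching factors, so differences between schools that those factors explain contribute less to the true sampling error of the treatment contrast. A model without those factors leaves their variance in the school random effect and carries it into the standard error. It analyses the trial as if schools had been allocated without restriction.

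If the factors predict walking distance, the interval for the between-group difference is too wide and the test conservative. The matching would then balance the arms without delivering its gain in precision. Because the fixed and random effects are spelled out in the article, a later document that added these terms would be changing the published primary model. It is better settled now.

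**Working it through.** **Inputs.** Sample size and power calculation gives SD 90 m, ICC 0.2, baseline–post correlation 0.60, 30 schools with 7 analysed students each, a target of 80 m and a 5% level (taken as two-sided). The share f of between-school variance that the matching explains is in neither the design nor the analysis text. It is an assumption here, with range 0–50%.

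**The plan's own figure.** The plan states: "This sample size will be enough to detect an MCID of 80 m with 90% power at a 5% significance level". On its inputs, comparing the arms at 6 months only:
- Design effect = 1 + (7 − 1) × 0.2 = 2.2.
- SE = 90 × √(2 × 2.2/105) = 18.42 m.
- Power for 80 m is 99.1% (normal) or 98.7% (t, 28 df).

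The 90% is therefore not reproduced, but it is exceeded. The recruitment target does reproduce: 210/(1 − 0.30) = 300.

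**Standard error with matching accounted for.** The between-school variance is 0.2 × 90² = 1620 and the within-school variance 0.8 × 90² = 6480. With 15 schools per arm,

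SE(f) = √[(2/15) × ((1 − f) × 1620 + 6480/7)].

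The stated model reports about SE(0) = 18.42 m whatever f is. Its actual type I error is roughly 2 × P(Z > 1.96 × SE(0)/SE(f)).

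| Share f (assumed) | True SE, m | Type I error, stated model | 95% half-width, stated model (28 df) | Adjusted, 26 df | Adjusted, 14 df |
|---|---|---|---|---|---|
| 0% | 18.42 | 5.0% | 37.7 | 37.9 | 39.5 |
| 10% | 17.83 | 4.3% | 37.7 | 36.6 | 38.2 |
| 30% | 16.57 | 2.9% | 37.7 | 34.1 | 35.5 |
| 50% | 15.21 | 1.8% | 37.7 | 31.3 | 32.6 |

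The 26 df column corresponds to two fixed school-level terms, such as cohort and a two-level school type. The 14 df column corresponds to an analysis of 15 pair differences. The t quantiles are 2.048 (28 df), 2.056 (26 df) and 2.145 (14 df).

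**Break-even at 14 df.** Adjustment helps once f exceeds (1 − (2.048/2.145)²) × (1620 + 925.7)/1620 ≈ 0.14.

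**Simulation check.** With 4,000 runs per scenario and school effects constant over time, coverage of the stated model's 95% interval for the 6-month difference was 95.4% at f = 0, 97.4% at 30% and 97.8% at 50%. This agrees with the table in direction and rough size.

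**Group-by-time contrast.** Time-constant school and pair effects cancel in the difference in change. The residual variance is (1 − 0.60) × 8100 = 3240, so the variance of a change is 6480. SE = √(2 × 6480/105) = 11.1 m, and the half-width is about 21.9 m. In simulation, coverage was about 95% at every pair correlation. A pair-level analysis on 14 df was slightly wider, at about 23.4 m.

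**Power.** At 80 m, power is about 98% or more with either analysis at every f. As an illustration only, take 44 m, the top of the adult range that the plan cites. Power is then about 64–66% under the stated model. With adjustment it is 70–72% at f = 30% and 77–80% at 50%, each range running from 14 to 26 df.

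**The case against.** The strongest objection is that the size of the gain is unknown. The plan promises matching only as closely as possible, on four ordered factors, with five pairs in the first cohort. Nothing in it shows that walking distance differs between school types. Schools for specific purposes and specialist support classes are described in the same terms, as serving moderate-to-high learning and support needs. Below a share of about 0.14, a pair-level analysis on 14 df is the less precise one. This stands, and it is why the point is conditional.

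Two stronger readings are tempting, and the documents support neither:
- A reader might infer that the interval is certainly too wide. No pair correlation is given, and the change contrast is not widened at all. The conservatism attaches to the difference at follow-up, which the plan does commit to reporting.
- A reader might infer that the trial is underpowered. At its own target it is not.

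It is also fair to say that the error is one-sided: no bias and no excess of false positives. The calculation further assumes school effects constant over time. If half the school variance were specific to a time point (an assumption), simulated coverage at a 30% share was 95.8% rather than 97.4%, so the conservatism shrinks.

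Leaving covariates to the analysis plan is the weakest objection, since the article lists the model's terms explicitly.

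**Conclusion.** The point holds in conditional form. The stated model does not reflect the restricted randomisation. If matching explains 30–50% of between-school variance, the standard error of the 6-month difference is reported as 18.4 m when 16.6–15.2 m would be right, and the nominal 5% test runs at about 3–2%. If matching explains 0–10%, there is little or nothing to gain. These figures rest on the plan's SD, ICC and cluster size, on the assumed share, and on time-constant school effects. The consequence is lost precision on the reported difference, not a threat to validity or to power for 80 m. The change is worth making because it is nearly free and brings the analysis into line with the design.

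**What to change.** Amend Statistical analyses to add the randomisation factors to the primary model before any unblinded analysis, in one of two ways:
- a random intercept for matched pair, with school nested in pair; or
- fixed effects for cohort and the main matching factors, at least school type.

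Either is preferable to 15 fixed pair effects. Cohort is constant within a pair, so a pair intercept already absorbs its time-constant part.

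The cost is one sentence of model wording, a few school-level degrees of freedom, and a slight loss of precision if matching proves uninformative (37.9 against 37.7 m half-width at 26 df). The random-pair version needs its degrees-of-freedom method stated. With balanced pairs, a method that follows the design may return about 14 df, in which case the 14 df column applies. Fixed factors keep more degrees of freedom but may capture a smaller share of the variance than the pairs do.

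### The reported 6-month LS mean difference leaves each arm's baseline mean free, so it is not adjusted for baseline distance, and the text does not say whether it or the group-by-time contrast is the primary test

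*Protocol article*

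**What the plan says.** All references are to the Protocol article. Under Statistical analyses, the fixed effects are group, time and their interaction: "The models will be used to assess the impact of group (B2La or control), time", and then "time (treated as categorical with levels baseline, 6 months and 9 months) and the group-by-time interaction". The random part has an intercept for participant and "a random intercept for school to account for the clustered design". The time point is fixed: "The primary endpoint of the study will be 6 months from baseline". The effect to be reported is also fixed: "Least square mean differences between the treatment groups will be presented at both follow-up time points, with 95% CIs and p values".

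The section does not enter baseline distance as a covariate, does not set the arms' baseline means equal, and does not define the effect as a difference in change.

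Under Sample size and power calculation, the simulation inputs taken from the pilot are a "baseline post-test correlation of *r*=0.60, SD of 90 m and an ICC of 0.2". The stated result is 90% power at the 5% level for 80 m, with 30 schools of seven. Under Blinding and randomisation, schools are randomised after baseline assessment, one from each matched pair to each arm.

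**The concern.** When baseline is a level of the outcome and each arm has a free mean there, the baseline data tell the model nothing about the difference between arms at 6 months. That difference is estimated from the 6-month data, and whatever imbalance arose by chance at baseline is carried along in it. With 15 schools per arm, moderate imbalance in walking or pushing distance is ordinary. The matching factors are school type, sector, location and educational advantage; baseline distance is not among them.

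The same model also yields the group-by-time contrast at 6 months, which is the difference between arms in change from baseline. That contrast does account for baseline, and it has a different estimate, standard error and p value. The section names the interaction and then promises the LS mean difference, without saying explicitly which one tests the primary hypothesis. At stake are precision and a single, pre-stated primary contrast.

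**Working it through.** **Inputs** (Sample size and power calculation; Blinding and randomisation): SD 90 m, ICC 0.2, r = 0.60, 15 schools per arm, 7 analysed students per school, effect 80 m, alpha 5%. The text does not give sidedness or say whether 90 m is the SD of a score or of a change. I assume a two-sided test and the SD of a single score.

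**The plan's own figures first.** Recruitment reproduces: 30 × 7 = 210, and 210/0.70 = 300. The 90% power does not. Power for 80 m, using t with 28 df (normal approximation in brackets):

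| Analysis | SD used | SE | Power at 80 m |
|---|---|---|---|
| Raw 6-month difference | 90 | 18.42 | 98.7% (99.1%) |
| Difference in change | 90√(2(1−0.6)) = 80.5 | 16.48 | 99.7% (99.8%) |
| Baseline-adjusted | 90√(1−0.6²) = 72 | 14.74 | 99.95% (99.97%) |

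None gives 90%, so how r entered the simulation cannot be recovered.

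**Unadjusted SE.** Between-school variance is 0.2 × 8100 = 1620; within-school variance is 6480. Var = (2/15)(1620 + 6480/7) = 339.4, so SE = 18.42 m.

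**Adjusted SE.** If r = 0.60 holds for school effects and for students within schools, the correlation of school means is 0.60. SE = 18.42 × √(1 − 0.36) = 14.74 m: 20% smaller, with 36% less variance.

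The gain is larger if school effects are stable over time. With a fully constant school effect, which the single school intercept implies, the within-school correlation is (0.6 − 0.2)/0.8 = 0.5. The correlation of school means is then (1620 + 3240/7)/(1620 + 6480/7) = 0.82, and the SE is about 10.6 m. That stability is an assumption, not a figure from the article.

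**Power at 44 m**, the top of the adult MCID range the article cites (28 df): 63.5% unadjusted (44/18.42 = 2.39) and 82.2% adjusted (44/14.74 = 2.99). A simulation of 10,000 trials analysed at school level gave 63.5% and 81.1%.

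**Effect of imbalance.** A one-SE baseline difference (18.4 m) moves the unadjusted estimate by 0.60 × 18.4 ≈ 11 m, or by 0.82 × 18.4 ≈ 15 m with a constant school effect. In simulation the unadjusted estimate correlated about 0.60 (0.82) with the baseline difference; the adjusted estimate correlated about 0.

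**Model check.** The stated model was fitted to one simulated complete data set (30 × 7, three visits, true effect 80 m). The 6-month LS mean difference was 97.34 m, the same as the raw difference in 6-month means (97.34 m). The chance baseline difference was 32.14 m. The group-by-time contrast in those data is 97.34 − 32.14 = 65.20 m. One fit thus offers two answers, 97 m and 65 m.

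**The case against.** The strongest reply is that the design already has precision to spare. Power of 90% for 80 m on 28 df implies an SE of about 80/(2.048 + 1.313) = 23.8 m, and the unadjusted SE at the stated inputs is 18.4 m. This stands. A reader might infer that the analysis is less precise than the sample size assumed, or that the trial is underpowered; the article's figures support neither. A shortfall at 80 m appears only with a larger SD. For example, treating the pilot's 131 m as the SD of a score gives 82% unadjusted and 95% adjusted, but the article attaches 131 m to the pilot's change and states 90 m for the sizing.

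A reader might also infer that the sample size depends on r = 0.60. It is a listed input, but since 90% does not reproduce with or without it, that dependence cannot be shown.

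The remaining objections stand in part:
- The unadjusted difference is unbiased under randomisation and its interval already allows for chance imbalance. Imbalance and imprecision are therefore one harm, not two.
- Pair-matching may make typical imbalance smaller than 18.4 m if the matching factors predict distance. The calculation ignores matching.
- The 44 m figure is from adults with chronic conditions and is not the design target.
- With the 30% loss allowed for, baseline does enter through the participant intercept, so the equality with the raw difference is exact only for complete data.
- If the group-by-time contrast is the intended test, baseline is accounted for. The article does not say so, and the effect it promises with interval and p value is the LS mean difference. The article itself states the model and the reported effect, so this is not merely detail left to an analysis plan.

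**Conclusion.** The point holds as one of efficiency and clarity. As written, the reported 6-month contrast is not adjusted for a baseline measured before randomisation, and it sits beside a different contrast with no explicit statement of which is primary. At SD 90 m, ICC 0.2 and 30 × 7, adjustment lowers the SE from about 18.4 m to 14.7 m, provided r = 0.60 holds at both levels. The difference detectable with 90% power falls from about 62 m to 50 m. The consequence is a wider interval than necessary, and it matters most if the true effect is well below 80 m. It does not threaten the stated target and does not bias the estimate.

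**What to change.** Replace the fixed-effects sentence with one of two forms, keeping the participant and school intercepts:

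1. Time (baseline, 6 and 9 months) plus group-by-time terms at 6 and 9 months only, with no group effect at baseline. This is valid because randomisation follows baseline assessment.
2. Distance at 6 and 9 months as the outcome, with group, time, group-by-time and baseline distance as a covariate.

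Then state that the baseline-adjusted difference between arms at 6 months is the single primary contrast, and that its estimate, 95% CI and p value are the primary result.

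The cost is a sentence or two of wording, made before the data are unblinded and recorded in the trial registry, where the article says amendments will appear. The baseline measurement is already collected, and the sample size need not change.
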